## Abstract

**Background:**

Anterior cervical discectomy with interbody fusion cages is considered the standard surgical procedure in patients with cervical disc herniation. However, PEEK or metal cages have some undesirable imaging characteristics, leading to a search for alternative materials not creating artifacts on images; silicon nitride ceramic. Whether patients treated with silicon nitride ceramic cages have similar functional outcome as patients treated with PEEK cages is not known. We present the design of the CASCADE trial on effectiveness of ceramic cages versus PEEK cages in patients with cervical disc herniation and/or osteophytes.

**Methods/Design:**

Patients (age 18–75 years) with monoradicular symptoms in one or both arms lasting more than 8 weeks, due to disc herniation and/or osteophytes, are eligible for the trial. The study is designed as a randomized controlled equivalence trial in which patients are blinded to the type of cage for 1 year. The total follow-up period is 2 years. The primary outcome measure is improvement in the Neck and Disability Index (NDI). Secondary outcomes measures include improvement in arm pain and neck pain (VAS), SF-36 and patients' perceived recovery. The final elements of comparison are perioperative statistics including operating time, blood loss, length of hospital stay, and adverse events. Lateral plane films at each follow-up visit and CT scan (at 6 months) will be used to judge fusion and the incidence of subsidence. Based on a power of 90% and assuming 8% loss to follow-up, 100 patients will be randomized into the 2 groups. The first analysis will be conducted when all patients have 1 year of follow-up, and the groups will be followed for 1 additional year to judge stability of outcomes.

**Discussion:**

While the new ceramic cage has received the CE Mark based on standard compliance and animal studies, a randomized comparative study with the golden standard product will provide more conclusive information for clinicians. Implementation of any new device should only be done after completion of randomized controlled effectiveness trials.

## Background

Since the introduction of anterior approach to the cervical spine by Cloward [1] and Smith [2], a dispute has arisen about the best surgical treatment. The purpose of all anterior cervical surgical procedures is removal of the intervertebral disc in order to decompress the nerve root and alleviate radicular pain and/or myelopathy. However, cervical instability and segmental collapse with recurrent radicular pain has been documented after anterior discectomy. For this reason, most surgeons perform anterior discectomy with interbody fusion (ACDF) although there is controversy about the benefits of adding interbody fusion to the cervical discectomy technique [3-9].

Anterior discectomy with fusion (ACDF) using bone graft in dowel or block form can have complications associated with graft collapse and can be associated with pain at the donor site if the graft is harvested from the iliac crest [10]. Interbody fusion using metal or plastic cages to contain and reinforce bone graft has been shown to have several advantages over bone blocks [11]: 1) using a cage allows the surgeon to fill the space without harvesting bone from the iliac crest in most cases; local bone or a bone graft substitute can be used instead; 2) the strength of the cage material ensures preservation of the disc height; bone blocks can crumble, decreasing the disc height with consequent neuroforaminal stenosis; and 3) using a cage saves time in the operating room and reduces blood loss. If there is no iliac crest bone graft harvest, there is less postoperative pain, as well.

Both plastic and metal cages have disadvantages as well. The principal plastic material, polyetheretherketone (PEEK), is hydrophobic and a mild chronic fibrous tissue reaction develops around the implant [12]. PEEK is invisible on imaging and therefore dislodgement and subsidence are difficult to determine. The two most commonly used metals, stainless steel and titanium distort magnetic resonance imaging (MRI) and CT scans, making determination of fusion and evaluation of degeneration difficult[13,14]. At present, ACDF with a PEEK cage is considered the golden standard for cervical disc herniation by many surgeons [15,19].

Recently, ceramic materials have been evaluated as alternatives for interbody fusion devices. The cortical ring of the new device is manufactured by study sponsor Amedica Corporation (Salt Lake City, Utah) from its proprietary “MC^2^” silicon nitride (Si_3_N_4_) ceramic. MC^2^ silicon nitride ceramic is a hydrophilic negative charged ceramic, which means that fluid (blood with nutrients) and proteins attach to the material, facilitating bone cell adherence and incorporation of the material in the surrounding bone. Cancellous Structured Ceramic (CSC) is a porous version of the same MC^2^ silicon nitride ceramic (Figure 1). Therefore, the entirety of this device is manufactured from identical material. The CSC material fills the center hole for the purpose of providing a scaffold for bone ingrowth. Because the surgical technique of this device does not involve harvesting autograft for packing into the pores of the porous trabecular structure, these implants afford the possibility of avoiding harvesting iliac crest autograft with attendant benefits of avoiding patient co-morbidities. Moreover, the silicon nitride material has desirable imaging properties. It is visible (like cortical bone) but does not create an artifact on CT or MR images (Figure 2).

**Figure 1 F1:**
[figure not shown]
Valeo C+CSC cervical interbody fusion device.

**Figure 2 F2:**
[figure not shown]
Silicon nitride, titanium, PEEK and trabecular metal imaging characteristics in a human cadaveric vertebra (unpublished data).

The Valeo C+CSC cage has received the CE Mark based on preclinical testing and standards compliance, but has not been evaluated in a clinical study. Good clinical practice means that every new device should be compared to the golden standard prior to implementation of the device on a large scale. Therefore, it is necessary to perform a randomized controlled effectiveness trail on Valeo C+CSC versus PEEK cages. In the CASCADE (CAncelous Structured Ceramic Arthrodesis DEvice) trial, we will randomly and blindly compare anterior discectomy with ceramic cages versus anterior discectomy with PEEK cages. In this equivalence trial, we hypothesize similar effectiveness and no difference in clinical improvement between the ceramic cage and the PEEK cage as measured with the Neck Disability Index (NDI). Moreover, radiological properties will be documented focusing on fusion and subsidence.

## Methods/design

The study is designed as single center randomized controlled trial in which patients will be blinded for the allocated treatment. The follow-up period will be 2 years. All patients between 18 and 75 years old with monoradicular symptoms in one or both arms lasting more than 8 weeks are eligible for the trial. MRI must confirm cervical disc herniation and/or osteophytes in accordance with clinical symptoms. Additional inclusion and exclusion criteria are listed in Table 1.

**Table 1 T1:** Selection criteria for trial eligibility

**Inclusion criteria**	
	• Age 18-75 years
	• Radicular signs and symptoms in one or both arms (i.e., pain, paresthesia or paresis in a specific nerve root distribution) or symptoms and signs of acute or chronic myelopathy
	• At least 8 weeks prior conservative treatment (i.e., physical therapy, pain medication)
	• Radiographic diagnosis of cervical disc herniation and/or osteophyte at 1 level (C3-C4 to C7-T1) in accordance with clinical signs and symptoms
	• Ability and willingness to comply with project requirements
	• Written informed consent given by the subject or the subject's legally authorised representative
**Exclusion criteria**		
	• Previous cervical surgery (either anterior or posterior)	
	• Increased motion on dynamic studies (> 3 mm)	
	• Severe segmental kyphosis of the involved disc level (> 7 degrees)	
	• Patient cannot be imaged with MRI	
	• Neck pain only (without radicular or medullary symptoms)	
	• Infection	
	• Metabolic and bone diseases (osteoporosis, severe osteopenia)	
	• Neoplasm or trauma of the cervical spine	
	• Spinal anomaly (Klippel Feil, Bechterew, OPLL)	
	• Severe mental or psychiatric disorder	
	• Inadequate Dutch language	
	• Planned (e)migration abroad in the year after inclusion	

Patients are referred by a neurologist with MRI of the cervical spine. During the first visit to the neurosurgical outpatient clinic, the patient’s history and a standard neurological examination will be documented. Based on our selection criteria, the neurosurgeon decides whether a patient is eligible for the trial.

### Informed consent and patients’ safety

The patient’s written informed consent is obtained. The patient will be notified that they are free to withdraw their consent at any time. An independent physician has been appointed to answer patient questions and monitor the study, when necessary. Adverse events or complications will be monitored and followed up until stable or resolved. The project will be conducted according to the guidelines of Good Clinical Practice. The study has been reviewed and approved by the Medical Ethics Committee (METC) of Southwest Holland.

### Randomization procedure

In order to eliminate confounding factors, the study is designed as a randomized controlled trial. Patients will be randomly allocated to the Valeo C+CSC or PEEK cages. Randomization will take place in the operating room within 6 weeks after inclusion. A randomization list was prepared by the data manager. A random numbergenerator was used to create the allocation sequence of blocks of 4, 6, and 8 to ensure equal distribution of the randomized treatments. The data manager, who is not involved in the selection and allocation of patients, prepared numbered, coded, sealed envelopes containing the treatment allocation. In the operating room, after induction of anaesthesia, the surgeon will open the next numbered envelope and the allocated treatment will be performed. Patients will be kept blinded for the allocated treatment for 1 year.

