### Surgical intervention

All patients will be operated by the authors MA or JW, who both have extensive experience in cervical spine surgery and this ACDF technique. The patients will be positioned supine with their neck in neutral position or slightly extended under general anaesthesia. The affected cervical disc level will be verified with fluoroscopy. A small transverse incision will be made on the right side. Medial to the carotid sheath, the pre-vertebral space will be opened and the anterior cervical spine will be exposed. Caspar spreader and 2 distraction pins will be placed in the affected segment. A standard anterior discectomy with the aid of loupe magnification or microscope (depending on the surgeon’s preference) will be performed in all cases. The posterior longitudinal ligament will be opened and the nerve root and dura will be decompressed adequately. Once the anterior discectomy has been performed, a PEEK interbody cage (Medicrea Manta, Lyon, France) (group 1) filled with local bone[20] obtained from removal of osteophytes, or the Valeo C+CSC spacer (Amedica Corporation, Salt Lake City, Utah) (group 2) will be placed within the intervertebral space under fluoroscopic guidance. The CSC core should be smeared with blood obtained by scratching the end plate after the disc space is prepared. No supplemental fixation (e.g., cervical plate) will be used in the procedure. If required, a vacuum drain will be placed and the wound will be closed in layers.

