3) Pain intensity, measured by Visual Analogue Score (VAS) of arm and neck. The VAS of arm pain will measure the experienced pain intensity in the arm during the week before visiting the researcher. Pain will be assessed on a horizontal 100 mm scale varying from 0 mm (no pain) to 100 mm (worst pain imaginable). Patients do not see the results of earlier assessments and will score the pain experienced at the visit. Since many patients with radicular arm pain have neck pain as well, we will also measure the intensity of solitary neck pain. Reliability, validity and responsiveness of VAS have been shown [28].

4) Perceived recovery: Likert Scale is a 7-point scale measuring the perceived recovery, varying from ‘complete recovery’ to ‘worse than ever’. This outcome scale has been used in previous studies and has been shown to be valid and responsive to change [29]. “Complete recovery” and “almost complete recovery” are defined as good result.

5) Radiological outcome: Anterior/posterior, and lateral views of the cervical spine will be performed at each visit. Displacement or subsidence of the device will be assessed by using the lateral radiograph. Only a change of >3 mm will be considered clinically significant due to the margin of error in radiographic determination of displacement distances. Radiolucency at the cage-bone interface will be assessed as either present (if extending 50% of the length of the cage) or absent using a standard lateral radiograph. To verify fusion, CT axial images at 2 mm slices will be taken at the 6 months visit only.

6) Other outcome measures: In addition to the outcomes measures, data will be captured on details of the surgical procedure and hospitalization such as type and size of implant, duration of surgery, estimated blood loss, operative and postoperative complications, day of mobilization, and duration of hospitalization. Adverse events and reoperations will also be recorded by the operating surgeon.

**Table 2 T2:** Data collection and outcome measures

**Measure**	**Pre-Op**	**Intra-Op**	**3 months**	**6 months**	**12 months**	**24 months**
Inclusion / exclusion criteria	x					
Product use, operative time, blood loss		x				
Neurological examination	x		x	x	x	x
Neck Disability Index, Arm Pain VAS, Neck Pain VAS, SF-36, Recovery Likert	x		x	x	x	x
Radiographs X-ray	x		x	x	x	x
CT scan				x		

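### As most naturally read, the envelope is opened before the discectomy, so the surgeon knows the cage during steps both arms share; this is avoidable, and bears chiefly on operating time and blood loss

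*Protocol article*

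**What the plan says.** Under Randomization procedure, the protocol article places the opening in theatre: "In the operating room, after induction of anaesthesia, the surgeon will open the next numbered envelope and the allocated treatment will be performed". Only patients are stated to be blinded, for one year.

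The Background, in the paragraph after Figure 2, describes the comparison: "we will randomly and blindly compare anterior discectomy with ceramic cages versus anterior discectomy with PEEK cages".

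The Surgical intervention section gives one sequence. A standard discectomy "will be performed in all cases", followed by the decompression: "The posterior longitudinal ligament will be opened and the nerve root and dura will be decompressed adequately". The two arms are first told apart after that: "Once the anterior discectomy has been performed, a PEEK interbody cage" or the ceramic spacer is inserted. The PEEK cage is filled with local bone "obtained from removal of osteophytes"; no bone filling is described for the ceramic spacer.

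The Outcome assessment section collects "type and size of implant, duration of surgery, estimated blood loss, operative and postoperative complications", and the Abstract lists operating time and blood loss among the items to be compared between arms.

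**The concern.** An operator cannot be blinded to a cage while inserting it. Knowledge of the arm before that moment serves no stated purpose, and it can influence how the shared part of the operation is done. Some of that part is left to judgement: the choice between loupe and microscope is the surgeon's, and the decompression is to be adequate, with no measured extent.

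The protocol also supplies an incentive that differs by arm. A surgeon who knows that a PEEK cage is coming needs osteophyte bone to fill it; one who knows that the ceramic spacer is coming does not. If this leads to more osteophyte removal in one arm, operating time and blood loss would differ for a reason that arises partly from when the allocation became known. A systematic difference in the decompression could also reach arm pain and the NDI. Patient blinding protects how patients report, but not how the operation was carried out.

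**Working it through.** The point contains no figure to recompute, so the check sets the relevant statements side by side.

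**1. When is the envelope opened?** The sentence under Randomization procedure gives the order: induction, then "the surgeon will open the next numbered envelope", then the allocated treatment. Strictly, induction fixes only the earliest moment.

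**2. What does the allocated treatment include?** By the Background, each arm's treatment is anterior discectomy with a given cage. The discectomy is thus part of what comes after the opening. No statement elsewhere in the article delays the opening. Opening before the discectomy is therefore an inference, but the natural one.

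**3. Where do the arms diverge?** In the Surgical intervention section everything up to and including the decompression is described once for all patients. The first arm-specific step is cage placement. The avoidable period of knowledge runs from opening the envelope to selecting the cage: approach, discectomy and decompression.

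**4. Does either arm need the allocation earlier?** The PEEK filling uses bone removed during the decompression, but that bone can be set aside until the cage is known. The ceramic core is smeared with blood from scratching the end plate, and the article puts this after disc space preparation, so it can also follow a later opening.

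**5. Which outcomes contain the shared period?**

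| Outcome | Depends on when the envelope is opened? |
|---|---|
| Duration of surgery | Yes; it includes the shared phase, whose conduct is in the operator's hands |
| Estimated blood loss | Yes; it includes the shared phase, and it is an estimate |
| Operative complications | In part; only those arising in the shared phase |
| Length of stay, postoperative complications | Little, and only indirectly |
| Adverse events and reoperations as recorded | Little; the operating surgeon records them and knows the cage either way |
| NDI | Only indirectly, through a difference in the decompression; it is completed by blinded patients |

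**6. Size.** The article gives no mean or spread for operating time or blood loss, no measure of decompression, and no relation between decompression and NDI. No magnitude can be calculated. The change proposed below leaves the sample size of 100 as it is.

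**The case against.** The strongest objection is that the article never says the envelope is opened before the discectomy. It fixes an earliest time, and a condensed article may leave the exact operative moment to the full protocol, which is not shown. This stands as a caution on wording. It does not remove the point, because the order of the sentence and the definition of the treatments both favour early opening.

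Second, the technique is standard, two experienced surgeons perform it, and patients who complete the NDI are blinded up to the one-year analysis. A reader might infer that the bias passes directly into the primary outcome. The documents do not support that: nothing in them shows that decompression would differ by arm. The route is plausible, but it is not demonstrated.

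Third, a later opening does not blind the surgeon from insertion onward. A reader might infer that all perioperative outcomes are compromised by the timing. They are not; length of stay and the recording of adverse events would be much the same under either timing.

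Fourth, a reader might infer that early opening creates deviations when a randomised patient turns out not to be able to receive a cage. The article describes no such patients and gives no frequency, so this remains hypothetical.

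Fifth, the need for bone could be a reason for early knowledge. The article does not offer that reason, and setting bone aside meets the need.

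Finally, the present scheme protects allocation concealment well: an uninvolved data manager prepared sealed, numbered envelopes, and they are opened in theatre. That is correct, and concealment is not in question here.

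**Conclusion.** The point holds as a modest, avoidable source of performance bias. On the natural reading, the operator knows the arm throughout an approach and decompression that the article describes identically for both groups, with an arm-specific reason (bone for the PEEK cage) to work differently. It bears chiefly on duration of surgery and estimated blood loss. An effect on the NDI through the decompression is possible. Neither the size nor the direction of any effect can be derived from the document.

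The conclusion rests on two assumptions: that the envelope is in practice opened soon after induction, and that the full protocol does not already set a later moment. If it does, only the article's wording needs correcting. The change is worth making because it is cheap; nothing here shows that the primary comparison is invalid.

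**What to change.** For patients not yet operated on, state under Randomization procedure, in words such as: *The surgeon opens the next envelope only when discectomy and decompression are complete, immediately before the cage is selected. Any bone already removed is set aside until then in every patient. The time of opening is recorded.* The recorded time allows duration of surgery to be split into a shared part and a cage-specific part.

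The costs are small. Both cages must be ready in theatre for each operation, removed bone is kept briefly in all patients, and the two surgeons need a short briefing. Because inclusion began in December 2011, some patients may already have been treated under the present procedure. Patients treated before and after the change must be distinguishable in the operating-time comparison. Allocation concealment is unaffected. The change does not blind the surgeon at insertion or in the later recording of adverse events, and should not be described as doing so.

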### Outcome assessment

Baseline assessments include demographics, work status, smoking status, neck and arm pain, history of neck trauma, medical history, pain medication, body mass index, and neurological signs and symptoms. A general physical and neurological examination is performed before the patient is enrolled into the study and will be repeated at each subsequent visit.

We will assess the below described validated outcome parameters. Patients will not be informed about their previous scores. Follow-up examinations will take place by the surgeon at 3 months, 6 months, 12 months, and 24 months after randomization. The schedule of follow-up visits, radiographic studies and outcomes measures is included in Table 2. The following measures of outcomes will be used:

1) Neck Disability Index (primary outcome measure): The NDI is a patient-completed 10-item questionnaire on 3 different aspects; pain intensity, daily work related activities and non-work related activities. Each item is scored from 0 to 5 and the total score ranges from 0 (best score) to 50 (worst score). The NDI is a modification of the Oswestry Disability Index and has been shown to be reliable and valid for patients with cervical pathology [21,22] and has been validated in the Dutch language [23].

2) Short-Form 36 (SF-36): The SF-36 [24] is a generic health status questionnaire that can easily be filled out by the patient at home. The questionnaire consists of 36 items on physical and social status of the patient subdivided in 8 domains; 1) physical functioning, 2) physical restrictions, 3) emotional restrictions, 4) social functioning, 5) somatic pain, 6) general mental health, 7) vitality and 8) general health perception. The questions are scored on a scale of 0 (worst health) to 100 (ideal health). This questionnaire has been used frequently and is validated in surgical studies on spine pathology [25,26].The Dutch language version has also been validated [27].

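### Patient blinding is promised for 1 year only, so the 24-month patient-reported outcomes, which are meant to show whether results last, are not protected by blinding

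*Protocol article*

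**What the plan says.** The protocol article gives the length of the patient blind twice. The Randomization procedure section says "Patients will be kept blinded for the allocated treatment for 1 year". The abstract (Methods/Design) puts the blind and the follow-up side by side: "patients are blinded to the type of cage for 1 year. The total follow-up period is 2 years". The opening of the Methods/design section mentions blinding without a time limit ("randomized controlled trial in which patients will be blinded for the allocated treatment").

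The abstract states the purpose of the second year: "the groups will be followed for 1 additional year to judge stability of outcomes".

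Visits are timed from randomization (Outcome assessment: "Follow-up examinations will take place by the surgeon at 3 months, 6 months, 12 months, and 24 months after randomization"), and randomization itself is done in theatre ("Randomization will take place in the operating room within 6 weeks after inclusion"). The primary outcome is the patient's own report ("The NDI is a patient-completed 10-item questionnaire on 3 different aspects"). The Table 2 row "Neck Disability Index, Arm Pain VAS, Neck Pain VAS, SF-36, Recovery Likert" is marked preoperatively and at 3, 6, 12 and 24 months.

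The Sample size and data analysis section places the first analysis at the point where the 1-year data are complete. It adds a repeated-measures analysis of variance of the NDI and does not list the visits that enter it.

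**The concern.** Blinding patients protects outcomes that depend on how patients judge and report their own condition. Here that covers the primary outcome and every clinical scale in Table 2. After 1 year the plan no longer promises that protection, yet it asks for the same questionnaires once more and gives the answers a purpose of their own.

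What is at stake is the reading of the second year. If the arms drift apart between 12 and 24 months, the cause may be a real late difference between the cages or a change in reporting among patients who know which cage they have. The reverse is also possible: a real late loss of benefit in one arm could be hidden if patients who know their cage report more favourably. The Discussion raises the possibility that the new cage improves clinical outcome, so an expectation that favours one arm is plausible, though the documents do not show that patients hold it.

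**Working it through.** The plan gives no figure on this point, so the check sets the schedule against the blind and then asks what the 24-month comparison can identify.

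**Step 1: visits against the blinded period.** The clock starts at randomization in the operating room.

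| Visit | Patient-reported scales collected | Within the promised 1 year of blinding? |
|---|---|---|
| 3 months | yes | yes |
| 6 months | yes | yes |
| 12 months | yes (primary time point) | at the end of the period |
| 24 months | yes | no, 24 − 12 = 12 months beyond it |

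One of the four postoperative assessments lies outside the blind. It is the only one in the second year, so every patient-reported value that bears on second-year stability is exposed.

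**Step 2: what a change after 12 months would measure.** Let D12 and D24 be the true between-arm differences in mean NDI at 12 and 24 months. At 24 months let p be the proportion of an arm that knows its cage, and s the average shift in score among those patients caused by knowing. If the blind holds at 12 months, the observed change in the between-arm difference is

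(D24 − D12) + (p_ceramic × s_ceramic − p_PEEK × s_PEEK).

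The second bracket is zero if nobody knows the cage, or if knowing shifts both arms equally. Otherwise it adds to the true change or offsets it. The trial observes only the sum, and the article describes nothing that would supply p or s. The two parts therefore cannot be separated at the analysis stage.

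**Step 3: the repeated-measures analysis.** If it uses 3, 6 and 12 months only, Step 2 does not apply to it. If it includes 24 months, the last interval may differ from the others in blinding status as well as in time, and the arm-by-time comparison carries the same ambiguity. The article does not say which is meant.

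**Step 4: the primary analysis.** The sample size rests on the change in NDI from before surgery to one year: SD 22%, margin 15% (7.5 points), 46 per arm, and 8% loss, so that 2 × 46 / (1 − 0.08) = 92 / 0.92 = 100. None of these inputs concerns 24 months, and no figure changes.

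**The case against.** The strongest reply is that this is an openly stated design choice and not an error. The primary analysis is at 1 year, the blind covers that year, and the second year is supplementary. No equivalence criterion is stated specifically for 24 months. All of that stands. It is why the point concerns the second-year aim only. It does not answer the point, because the article gives those data a purpose and no reason for ending the blind a year before they are collected.

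Several stronger readings are tempting and are not supported:

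- **A late 12-month NDI is given unblinded.** The 12-month visit falls at the end of the blinded year, so a reader might infer that a patient seen late answers the primary questionnaire unblinded. The text fixes no calendar date. The article also uses 1 year as the name of the primary time point, so the blind may equally run through that assessment. Visit windows and unblinding procedures are commonly left to the full protocol.
- **The 24-month data are open-label.** Nothing says that patients are told their cage at 1 year. The promise of concealment lapses, and that is all the text shows.
- **Patients will know the first results.** The article says when the first analysis is done, not that its result reaches patients.
- **The surgeon's role biases these scores.** The surgeon opens the envelope and performs the follow-up examinations. The forms, however, are completed by patients, and hospital staff supervise their collection. Who examines the patient is a separate matter, and changing the examiner would not restore the patient's blind.
- **The bias can be expressed as a share of the 7.5-point margin.** Any shift in NDI from knowing the cage would have to be invented, and that margin was used to size the 1-year comparison.

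**Conclusion.** The point holds in a limited form. Under the plan as written, blinding is not assured for any 24-month patient-reported outcome: NDI, arm and neck pain VAS, SF-36 and perceived recovery. A between-arm change after 12 months on these scales could not be attributed to the cages with confidence. The repeated-measures NDI comparison shares the problem only if it includes the 24-month visit.

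The extent is one of four postoperative assessments, in all patients still followed at that time. The size of any bias is unknown. It depends on how many patients learn their cage and on whether that knowledge affects reporting differently in the two arms, and the documents inform neither. The conclusion assumes only that some patients may learn their allocation once concealment is no longer promised. The planned 1-year primary analysis and the sample size are not shown to be affected. The change is worth making because it is cheap, not because the trial's main result is in doubt.

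**What to change.** In the Randomization procedure section, and correspondingly in the abstract, replace the 1-year limit with: *Patients remain blinded until their 24-month questionnaires are complete; any earlier disclosure is only for medical need and is recorded with its date.* The sentence without a time limit at the start of Methods/design then needs no change.

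For any patient who has already been told, record the date and label that patient's 24-month patient-reported data as unblinded.

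If the longer blind cannot be adopted, the minimum is to state that no disclosure occurs before the 12-month forms are complete. This settles the ambiguity at the primary time point but does not protect the 24-month data.

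**Cost.** The change is to protocol and patient-information wording. Sample size, visits and staffing stay as they are. Patients learn their cage type one year later, and those already enrolled need an updated information letter. Inclusion began in December 2011, so some patients may already have been told. They cannot be re-blinded, and for them the change brings labelling only.
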